### Excluded Criteria

2.3

Transient ischemic attack;Subarachnoid hemorrhage;History of severe liver or kidney diseases, mental illness, epilepsy, asthma, or obstructive pulmonary diseases;Occurrence of cognitive impairment prior to stroke;Severe communication barriers;Substance abuse or heavy alcohol consumption;Implanted cardiac pacemakers or other electronic devices.

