Modern pharmacological studies have shown that ATR can protect central neurons, enhance memory and learning functions, resist nerve cell apoptosis, and inhibit central cholinergic activity, leading to significant therapeutic effects (Wang et al. 2023, Xu et al. 2023). Herbal olfactory therapy (HOT) using traditional Chinese medicinal materials triggers biochemical reactions in the respiratory, nervous, and circulatory systems, influencing human emotions, physiology, and behavior (Zhang et al. 2021). The volatile oil of ATR can quickly penetrate the blood‐brain barrier to provide therapeutic benefits. Moreover, certain acupuncture points have been found to stimulate brain activity and cognitive function. For example, Suliao (GV25) is known for its ability to clear heat and improve mental clarity, while Yingxiang (LI20) can enhance energy flow and cognitive function. By applying essential oils to these specific acupoints, the absorption of the oils can be enhanced, leading to improved therapeutic outcomes.

Electroacupuncture therapy (EA) involves connecting an electroacupuncture device to acupoints in the neck area and has been used in the clinical treatment of cerebral ischemia with significant therapeutic effects. [name] proposed a novel treatment method for cerebrovascular diseases, which includes needling the bilateral Fengchi (GB20) and Gongxue to stimulate them with pulsed electric currents (Liu et al. 2017). This stimulation improves inadequate cerebral blood supply and enhances cerebral blood circulation. Electroacupuncture connecting the Fengchi (GB20) and Gongxue has shown noticeable effects in promoting meridian function, regulating metabolism, and improving limb and language functions in patients with head and neck diseases such as brainstem ischemia (Fu et al. 2023, Wang et al. 2009). This study aims to evaluate the clinical efficacy of electroacupuncture combined with ATR volatile oil inhalation therapy in treating PSCI. The research seeks to provide evidence that the integration of EA with ATR volatile oil inhalation therapy offers superior clinical benefits compared to single‐modality treatments for PSCI, through rigorous clinical investigation.

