### Inclusion Criteria

2.2

Stroke as per the Traditional Chinese Medicine (TCM) definition, presenting symptoms include unilateral paresis or paralysis, sensory deficits, speech impairment, and hemianopsia. PSCI diagnosis involves clinically significant deficits in at least one cognitive domain and severe disruption of instrumental ADLs/ADLs.The scores on the MMSE scale must adhere to the following criteria: Less than 17 points for individuals with illiteracy, less than 20 points for those with primary school education, and less than 24 points for individuals with a middle school education or higher.The age range is 45 to 70 years;No history of mental illness, clear consciousness, stable vital signs, and able to complete the scale assessment;Within 3–6 months post‐stroke, diagnosed as a patient in the recovery period of cerebral infarction (or cerebral hemorrhage) at admission;Signed informed consent by the patient or their family.

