#### Herbal Olfactory Therapy

2.6.3

The baseline characteristics of the enrolled patients will be similar to those described in Section 2.5.2 (as above). Following enrollment, participants will receive an immediate traditional Chinese medicine olfactory diagnosis treatment conducted by a single therapist to eliminate potential biases. The therapy will involve using essential oil from ATR in a rollerball inhaler, applied uniformly to specific acupoints (Figure 2A, Table 1, Suliao (GV25), bilateral Yingxiang (LI20) (Zabor et al. 2020)) to enhance cognitive awakening. Participants will be instructed to inhale the oil for 5 to 10 min, three to five times daily, for 4 weeks while maintaining steady and regulated breathing.

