#### Combination Group

2.6.4

The combination group will receive electroneutral acupuncture and olfactory therapy. The procedures were the same as in Sections 2.6.2 and 2.6.3.

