### Safety Monitoring

2.9

Acupuncture and olfactory therapy pose mild adverse effects. Acupuncture may cause pain, numbness, or bruising, while olfactory therapy may lead to allergic reactions or affect the liver or kidneys. Serious adverse events will be promptly reported, and patients experiencing such events will be withdrawn from the study. Adverse events will be documented on case report forms and reported to statisticians.

Adverse events (AEs) are typically classified into three severity grades: mild, moderate, and severe. Mild adverse events refer to symptoms that are tolerable to participants, requiring no specific intervention, and do not affect the trial progression or participant prognosis. Moderate adverse events involve clinically significant symptoms that are difficult for participants to tolerate, potentially necessitating trial discontinuation or medical treatment, and may impact disease recovery. Severe adverse events are life‐threatening conditions that could lead to permanent disability or mortality, requiring immediate trial termination and emergency medical intervention. During the treatment period, any adverse events must be documented in real‐time, investigated for causality, and promptly reported to the supervising physician for evaluation and management.

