## Discussion

3

PSCI is a form of cognitive dysfunction that can occur following a stroke. Two non‐pharmacological treatment methods that have gained attention for their minimal side effects are traditional Chinese medicine olfactory inhalation therapy and electric neck acupuncture. Electric acupuncture has been widely used in treating neurological conditions like cerebral ischemia, Alzheimer's disease, and Parkinson's disease (Cai et al. 2019, Shin et al. 2017, Kong et al. 2010). Electric neck acupuncture, a novel technique developed by [name], leverages the anatomical, physiological, and pathological features of the neck to treat neurological disorders effectively (Liu et al. 2017). While there is limited research on the efficacy of electric neck acupuncture for PSCI, TCM olfactory inhalation therapy focuses on enhancing cognitive function and emotional well‐being by stimulating the olfactory nerve in brain regions associated with the sense of smell. Ancient texts like the Divine Farmer's Materia Medica mention the therapeutic benefits of olfactory inhalation therapy for conditions such as senile dementia, stroke, and epilepsy. HOT works through the aroma molecules of plants, which are transmitted to the limbic system of the brain and even through the pores of the human body, penetrating into the deeper tissues, resulting in muscle relaxation and a pleasant emotional feeling. Studies have shown that the use of calamus volatile oil by gavage for three weeks can reduce nitric oxide synthase (NOS) in the brain and hippocampus of Alzheimer's disease mouse models, and significantly improve learning and memory dysfunction (Tian et al. 2012). Inhalation of eugenol over a 4‐week period enhanced learning memory by interfering with neurotransmitters in the olfactory system, thereby altering olfactory afferent signals (Shuai et al. 2021). Our study aims to explore the potential of traditional Chinese medicine olfactory inhalation therapy and electric neck acupuncture, either individually or in combination, as treatments for PSCI.

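### Allergic reactions are named as a risk of the olfactory oil, but known allergy to the oil is not an exclusion, although the liver and kidney risks named beside it are covered

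*Protocol article*

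**What the plan says.** **Hazard.** Section 2.9 (Safety Monitoring) states that "olfactory therapy may lead to allergic reactions or affect the liver or kidneys".

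**Exclusions.** Section 2.3 excludes transient ischaemic attack, subarachnoid haemorrhage and cognitive impairment that preceded the stroke. Its organ and airway item is "History of severe liver or kidney diseases, mental illness, epilepsy, asthma, or obstructive pulmonary diseases". The rest of the list is "Severe communication barriers;Substance abuse or heavy alcohol consumption;Implanted cardiac pacemakers or other electronic devices".

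**Inclusions.** The nearest item in Section 2.2 asks for "clear consciousness, stable vital signs, and able to complete the scale assessment". Nothing there concerns allergy, smell or the nasal airway.

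**Exposure.** In Section 2.6.3 the oil is rolled on the nasal acupoints of Table 1, and "Participants will be instructed to inhale the oil for 5 to 10 min, three to five times daily", for 4 weeks. Section 2.6.4 adds that "The combination group will receive electroneutral acupuncture and olfactory therapy".

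**Mechanism.** The Discussion says that olfactory therapy acts by "stimulating the olfactory nerve in brain regions associated with the sense of smell". The Introduction gives a second route: "By applying essential oils to these specific acupoints, the absorption of the oils can be enhanced". It also says that the volatile oil crosses the blood-brain barrier, and the Discussion adds passage through the pores into deeper tissue.

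**The concern.** The exclusion list already appears to screen by treatment hazard. Severe liver and kidney disease are on it, and both organs are named as at risk in Section 2.9. Asthma and obstructive lung disease fit an inhaled product, and implanted electronic devices fit electrical stimulation. Allergic reaction is named in the same sentence as the liver and kidney risks and has no counterpart. A patient whose allergy is known at screening could therefore be exposed repeatedly, on the skin and by inhalation, to the substance concerned.

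The secondary concern is sensitivity. The aim is to show that the combination is superior to either treatment alone, and combination versus electroacupuncture (EA) isolates what HOT adds. A participant who cannot smell contributes nothing to that contrast by the olfactory route. Table 2 schedules no smell measure, so such participants could not be identified after a null result.

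**Working it through.** **Step 1. Set hazards and treatment features against Section 2.3.**

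| Stated hazard or feature | Where | Item in 2.3 |
|---|---|---|
| Liver effects of HOT | 2.9 | Severe liver disease |
| Kidney effects of HOT | 2.9 | Severe kidney disease |
| Allergic reactions to HOT | 2.9 | None |
| Inhaled product | 2.6.3 | Asthma, obstructive lung disease |
| Electrical stimulation | 2.6.2 | Pacemakers, other devices |
| Olfactory route of action | Discussion | None |

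The article does not give its reasons for the lung and device items, so pairing them with treatments is my reading. The liver, kidney and allergy rows need no such reading, because one sentence in 2.9 names all three.

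**Step 2. Look for a criterion elsewhere.** Section 2.6.3 refers to Section 2.5.2 for patient characteristics, but 2.5.2 describes the random allocation table. If 2.6.2 was meant, the only condition there is no earlier psychotropic medication. Neither section adds an allergy or smell criterion.

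**Step 3. Which arms are exposed.** HOT and combination clearly are. Section 2.6.5 says that healthy participants also receive an olfactory treatment, and then refers to Section 2.6.1, the control regimen, which contains none. Section 2.6.6 sends the sham group to 2.6.5. Whether these two groups receive oil cannot be settled from the text, and the passages must be reconciled.

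**Step 4. What smell loss could do.** The article gives no figure here, so there is none to reproduce, and the sample size in Section 2.1 is not used. Let f be the share of participants who cannot smell and s the share of the HOT effect that works through smell. Neither is in the documents. The expected contrast becomes (1 − f·s) times its full size. A comparison with 80% power at two-sided 0.05 then has power Φ[(1.960 + 0.842)(1 − f·s) − 1.960].

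| f·s | Remaining effect | Power |
|---|---|---|
| 0 | 1.00 | 80% |
| 0.05 | 0.95 | 76% |
| 0.10 | 0.90 | 71% |
| 0.20 | 0.80 | 61% |
| 0.30 | 0.70 | 50% |

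For example, f = 0.10 with s = 0.5 gives f·s = 0.05 and a power of 76%. With s = 0 there is no loss at any f. These rows are assumptions, not estimates for this trial.

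**Step 5. Which contrasts are touched.** Combination versus EA is. HOT versus control is too, to the extent that background treatment is the same in both arms. Combination versus HOT isolates EA, and non-smellers are expected equally in both of its arms, so this dilution does not apply there.

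**The case against.** **Allergy.** The article is condensed, and Section 2.10 promises standard operating procedures for screening, where a hypersensitivity check could sit. Section 2.9 calls the adverse effects mild and provides for real-time recording, causality review, prompt reporting and withdrawal after serious events. Excluding asthma may also remove some allergic patients. Part of this stands: the harm may be rare and mild, and an unseen document may already contain the check. But the stated list covers two of three hazards from one sentence and omits the third. Adverse-event recording acts only after exposure, and asthma is not the same as known allergy to this oil.

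**Smell.** This objection is stronger. A reader might infer that the HOT arms depend on smelling, so that the effect is certainly diluted and a null result could not be interpreted. The article does not support that. It claims absorption at the acupoints, passage through the pores and entry across the blood-brain barrier, none of which needs smell. Randomisation should balance non-smellers across arms, so the issue is possible lost sensitivity and not bias. Estimating the effect in patients as they present is also a legitimate choice.

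A reader might also put the cost at 1.23 to 2.78 times the patients. Those factors are 1/(1 − 0.10)² and 1/(1 − 0.40)². They require 10% to 40% smell loss and an effect that is wholly olfactory, so they can serve only as an upper-bound illustration. Smell loss as high as 40% would also contradict any claim that screening for it costs few patients.

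**Conclusion.** The allergy gap holds. Sections 2.3 and 2.9 do not match: a hazard that the article names has no eligibility criterion, in at least two arms. This needs no prevalence figure and no assumption about mechanism. It does not show that harm is likely, because the documents give no frequency or severity for such reactions beyond calling the effects mild.

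The smell gap holds only as a secondary point. Patients without smell may dilute any smell-mediated part of the combination-versus-EA and HOT-versus-control contrasts. The amount depends on two unknown shares and may be near zero if the absorption routes dominate.

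Overall this is an inexpensive improvement to eligibility. It is not a flaw that undermines the trial.

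**What to change.** 1. Reconcile Section 2.3 with Section 2.9 by adding an exclusion for known hypersensitivity to Acorus tatarinowii oil or its components. Ask about it before randomisation and apply it to all arms, so that the groups stay comparable. The exact wording is for the investigators.
2. Reconcile Sections 2.6.5 and 2.6.6 with 2.6.1, so that it is clear which groups receive oil, and correct the reference to 2.5.2 in Section 2.6.3.
3. Add a history question on loss of smell or nasal obstruction, asked before randomisation in all patient arms. The investigators should state whether the answer excludes the patient or is only recorded. Self-report may be unreliable in a cognitively impaired population, so a carer's answer may help.

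The cost is one or two screening questions, a slightly narrower population and somewhat slower recruitment. If the smell item is only recorded, it costs no eligible patients but does not prevent dilution.

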### Randomization and Blinding

2.4

Using a random number table method, the PSCI participants in the trial will be randomly allocated to (1) the control group, (2) the EA group, (3) the HOT group, (4) the combination group, (5) the sham group, and (6) the healthy group, with 35 individuals in each group. Notably, the present study was designed as a separate cohort of healthy subjects to assess brain functional abnormalities in patients with PSCI using functional magnetic resonance imaging (fMRI) and to validate the effects of interventions such as acupuncture and ATR volatile oil therapy on brain function. Data from healthy people provide a baseline of normal brain function for the study, helping to identify pathological changes in stroke patients. The allocation process is concealed, and the assessors will be kept blinded to the participant's allocation. Participants are instructed not to discuss their research participation or experiences with the assessors during the evaluation period. Patients will be informed that they would receive either EA treatment, HOT, or both, without being informed about the number of acupoints or the specific stimulation sites.

Acupuncture and herbal treatments will be administered by licensed acupuncturists, while a qualified rehabilitation physician will train a research assessor to evaluate the efficacy of acupuncture. The research assessor and data analysts will remain blinded to group assignment, although participants will be informed during the informed consent process.

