**Methods:**

This parallel‐group, assessor‐blinded, randomized controlled trial will recruit 210 PSCI patients, randomly assigned to one of six groups: control, EA, HOT, combination therapy, sham therapy, or the healthy (ratio 1:1:1:1:1:1). All participants will receive standard cognitive training and basic medical care. The EA group will receive 4 weeks of electro‐acupuncture at specific acupoints. The HOT group will receive 4 weeks of aromatic inhalation therapy using Acorus tatarinowii volatile oil. The combination group will receive both interventions. The primary outcome measure is cognitive function, assessed using the Montreal cognitive assessment (MoCA) at baseline, week 4, and week 8. Secondary outcomes include the mini‐mental state examination (MMSE), functional magnetic resonance imaging (fMRI), near‐infrared spectroscopy (fNIRS), and anxiety assessment using the state‐trait anxiety inventory (STAI) at baseline and week 4. Data analysis will be conducted using a modified intention‐to‐treat approach.

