### Data Analysis

2.11

Researchers who are blind to the groupings will conduct data management and statistical analysis on the data acquired using the statistical software SPSS 22.0 (SPSS Inc., Chicago, IL, United States). Descriptive statistics will be utilized to depict the baseline characteristics of the two participant groups, with mean ± standard deviation for normally distributed continuous data and median and quartiles for non‐normally distributed continuous data. The normality of the data will be assessed using the Shapiro–Wilk test, and the homogeneity of variance will be assessed using the Levene test. One‐way analysis of variance (ANOVA) will be used for comparisons among multiple groups for normally distributed continuous data, while repeated measures analysis of variance will be used for within‐group pre‐ and post‐treatment comparisons. The Kruskal–Wallis test will be employed for non‐normally distributed continuous data. The significance level (α) for the statistical hypothesis tests will be set at *p* < 0.05, one‐tailed.

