In addition to the primary outcome measures, we also included some imaging examinations as secondary measures. fMRI is used to assess cerebral hemodynamics and identify activated brain regions to compare different groups (Logothetis 2008). fNIRS is a non‐invasive, portable, and cost‐effective method that measures changes in oxygenated and deoxygenated hemoglobin levels in the cerebral cortex using near‐infrared light, reflecting neural activity (Irani et al. 2007). fNIRS allows for convenient self‐control and observation of the brain during treatment, providing detailed insights into stimulated brain areas by acupuncture and Traditional Chinese medicine olfactory. Ultrasound Doppler is another non‐invasive method to examine cerebrovascular diseases by detecting hemodynamic and physiological changes in major intracranial arteries (Wan et al. 2022). These secondary measures help us understand participants' cerebral vascular function changes during treatment and offer preliminary evidence for further exploration of underlying mechanisms. Moreover, by comparing with the healthy population, this study more clearly revealed the abnormal brain function of patients with cognitive impairment after stroke and the effect of intervention on their brain function. This design not only enhances the scientific validity of the study results, but also provides a more reliable basis for clinical application.

The study design was limited to a single‐center study, resulting in a relatively small sample size. To enhance the robustness of the study, future studies should include more diverse cases from multiple centers. Additionally, the lack of a sham stimulation group as a control group due to controversies surrounding the need for sham acupuncture and its implementation is a limitation of this trial design. Subsequent experiments will delve into detailed basic research both in vitro and in vivo to uncover the molecular mechanisms behind HOT and EA treatment for enhancing cognitive function in stroke patients. While non‐pharmacological treatments show promise in addressing PSCI injuries, further extensive research and clinical trials are essential to validate their efficacy and safety. Therefore, the significance of this study lies in providing stronger evidence for the clinical application of these treatments.

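### The healthy group is listed as a randomised arm but is a separate, non-randomised cohort, and the only between-group tests stated take no covariates, so demographic differences could be read as stroke pathology

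*Protocol article*

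**What the plan says.** **Status of the healthy group.** Section 2.4 states that "the PSCI participants in the trial will be randomly allocated to (1) the control group", and the list of destinations ends with "6) the healthy group, with 35 individuals in each group". The Abstract likewise gives one equal allocation ratio over all six groups: "sham therapy, or the healthy (ratio 1:1:1:1:1:1". Yet section 2.4 goes on to say that "the present study was designed as a separate cohort of healthy subjects to assess brain functional abnormalities in patients with PSCI", using fMRI.

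**Purpose of the contrast.** Section 2.4: "Data from healthy people provide a baseline of normal brain function for the study, helping to identify pathological changes in stroke patients". The Discussion draws the conclusion in advance: "by comparing with the healthy population, this study more clearly revealed the abnormal brain function of patients with cognitive impairment after stroke".

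**Between-group method.** Section 2.11 says that one-way ANOVA "will be used for comparisons among multiple groups for normally distributed continuous data", and that the Kruskal-Wallis "test will be employed for non‐normally distributed continuous data". No covariate is named. The fMRI text in section 2.7.2 covers preprocessing, connectivity and independent component analysis, but gives no group-level model.

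**The concern.** Randomisation protects the comparisons among the five patient groups. It cannot protect a comparison of patients with volunteers, because being healthy is not something that can be allocated. Counting the healthy cohort as one of six randomised groups hides this, and it lets the cohort pass into a general multi-group test that makes no allowance for confounders.

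The interpretation is the part at risk. A patient-healthy difference in an imaging measure is to be taken as a sign of disease, and the healthy level as the target against which the effect of treatment on brain function is validated. If the volunteers differ from the patients in age, sex or education, part of the difference may reflect those characteristics. The apparent abnormality would be too large or too small, and a treatment could seem to restore, or fail to restore, a level that was never the right reference.

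**Working it through.** **1. Is the contrast randomised?** Set the statements of section 2.4 side by side: patients are randomly allocated to six groups including the healthy one, and the healthy group is a separate cohort of healthy subjects. Both cannot be true. Section 2.2 requires stroke, a low MMSE score and a time since stroke of 3 to 6 months, so nobody who meets it is healthy. Only the separate-cohort statement can be carried out. The Abstract's 210 patients (6 × 35) then become 5 × 35 = 175 patients plus 35 healthy subjects.

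**2. Does any stated method adjust?** One-way ANOVA and Kruskal-Wallis compare groups without covariates. Repeated-measures ANOVA is assigned to pre/post change within groups. No other between-group test is stated, and section 2.11 makes no exception for the healthy group.

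**3. How large could the effect be?** The documents give no figure to reproduce and no imbalance, so this is illustrative. Inputs:

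- Group size 35 (sections 2.1 and 2.4).
- Within-group SD of the imaging measure set to 1.
- *Assumed*: the healthy and patient groups differ by d SD on a covariate that correlates r with the measure within groups. The bias is b = d × r.
- No true patient-healthy difference, two-sided 5% test.

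Standard error = √(1/35 + 1/35) = 0.239 SD, with 68 degrees of freedom. The noncentrality is b / 0.239, and the rejection rate comes from the noncentral t distribution. For the six-group F test with only the healthy mean shifted, the noncentrality is 35 × b² × 5/6, on 5 and 204 degrees of freedom.

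| d | r | b (SD) | b / 0.239 | 35 v 35, t test | six-group F test |
|---|---|---|---|---|---|
| 0 | any | 0 | 0 | 5.0% | 5.0% |
| 0.25 | 0.2 | 0.05 | 0.21 | 5.5% | 5.3% |
| 0.5 | 0.3 | 0.15 | 0.63 | 9.5% | 8.0% |
| 0.5 | 0.5 | 0.25 | 1.05 | 17.8% | 14.3% |
| 0.8 | 0.5 | 0.40 | 1.67 | 37.8% | 33.0% |
| 1.0 | 0.5 | 0.50 | 2.09 | 54.1% | 50.7% |

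Section 2.11 sets the level at 0.05 one-tailed. With the bias in the tested direction, the one-tailed 35 v 35 rate runs from 7.5% (b = 0.05) to 66.5% (b = 0.50).

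**4. If a true difference exists.** A false-positive rate then has no meaning, but the bias remains: the estimate is off by b on average. The 35 v 35 column still applies, read as the chance that a nominal 95% confidence interval misses the true difference. Coverage falls from 100 − 5.5 = 94.5% at b = 0.05 to 100 − 54.1 = 45.9% at b = 0.50.

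**The case against.** The strongest reply is that this is a condensed article. Volunteer eligibility, matching and imaging covariates are commonly left to the full protocol or analysis plan. That stands: a reader might infer that the trial does not match its volunteers, but the article is only silent on this. What does not fall to this reply is what the article states: the two incompatible descriptions of the healthy group, a general between-group rule with no covariates, and the reading of differences as pathology.

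Other stronger readings also fail:

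- *This is the trial's only non-randomised comparison.* It is not; the within-group pre/post tests in section 2.11 are not randomised contrasts either.
- *The plan assigns ANOVA to the fMRI contrast.* Section 2.11 names neither imaging nor the healthy cohort. ANOVA or Kruskal-Wallis covers the contrast only as the general rule for comparing groups, of which the healthy group is counted as one.
- *The education-specific MMSE limits (17, 20 and 24) prove confounding.* They show that education matters for a cognitive score. They say nothing about imaging, and confounding also needs an actual imbalance, which the documents do not show.
- *The age range of 45 to 70 excludes the volunteers.* It stands in a list otherwise written for patients, so whether it covers them is unclear.
- *The error rate reaches 77%.* That arises for 35 healthy subjects against 175 pooled patients with a 0.5 SD bias, a contrast that no section plans.

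It is also fair to say that a null of no difference in brain function between volunteers and these patients is implausible, so bias in the size of the difference is the more realistic harm. Finally, section 2.6.5 has the healthy participants treated after entry, so only week 0 is an untreated reference. Covariate adjustment does not address that.

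**Conclusion.** The point holds in a limited form. Section 2.4 contradicts itself on whether the healthy group is randomised; in substance it cannot be. Followed as written, the plan compares it with patients by tests that take no covariates and reads the result as pathology, so differences in age, sex or education could be mistaken for effects of stroke.

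The size is unknown. It ranges from negligible (5.5% false positives at a 0.05 SD bias) to serious (54% at 0.5 SD, which takes a 1 SD imbalance and a correlation of 0.5), all under assumed inputs. With no imbalance the error rate stays at 5%.

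The consequence is confined to the interpretation of secondary imaging outcomes. A reader might infer that the primary result is compromised. The documents do not support that: the MoCA comparisons among the randomised patient groups, including combination therapy against either monotherapy, do not depend on the volunteers, provided the healthy group is kept out of them.

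**What to change.** - **Section 2.4, with the Abstract and section 2.1 to agree:** state that only the five patient groups are randomised, 1:1:1:1:1, and that the healthy group is a non-randomised reference cohort. Give patient and healthy numbers separately (175 and 35 on the present figures).
- **Section 2.11:** take the healthy group out of the multi-group ANOVA and Kruskal-Wallis tests. Analyse the patient-versus-healthy imaging contrast by linear regression on group, age, sex and education, with an estimate and confidence interval, reported as a non-randomised comparison.
- **Recruitment, where still possible:** apply the 45 to 70 age range to the healthy cohort and frequency-match it to the patients on sex and education. Adjustment relies on the groups overlapping on these characteristics; where they do not, the regression extrapolates.

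The cost is a few sentences, three routinely available covariates and one regression model. Matching may slow the recruitment of 35 volunteers slightly, and it cannot be done cleanly once they have been recruited; adjustment still can. Adjustment deals only with the covariates included, so the Discussion should say that patient-healthy differences may have other explanations than stroke.
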